### Psychological outcomes

Melanoma-related worry will be assessed using three items:
*How worried are you about getting melanoma someday?**How often does your worry affect your mood?**How often does your worry affect your ability to perform your daily activities?*

Each item will be assessed on a 5-point Likert scale: 1 = not at all, 2 = rarely, 3 = sometimes, 4 = often, 5 = almost all the time, and a mean score will be calculated.

Psychological distress and well-being will be assessed separately using the five-item version of the Mental Health Inventory (MHI-5) [29]. The MHI-5 is a subscale of the 36-item Short Form Health Survey (SF-36) comprising the following items: *How much of the time during the past month have you:*Been a very nervous person?Felt so down in the dumps that nothing could cheer you up?Felt calm and peaceful?Felt downhearted and blue?Been a happy person?

Response options are on a 6-point Likert scale ranging from 1 = never to 6 = all of the time. Items (c) and (e) above will be reverse-coded and the five scores then summated to a total subscale score in which higher scores indicate a worse health state and lower scores a better health state. Up to two missing values on the subscale will be imputed using the personal mean values from the completed items; otherwise the total score will be set to missing [30]. Each raw scale subscale score (ranging from 5 to 30) will be transformed to a 0 to 100 scale using the formula below, where the lowest possible raw score is 5 and the possible raw score range is 25:
$$ Transformed\ Scale=\frac{\left( Actual\  raw\  score- Lowest\ possible\  raw\  score\right)}{Possible\  raw\  score\ range}\times 100. $$

Intervention arm additional measures: the experience of the intervention, the psychological impact of undergoing genomic testing and receiving the results, and communication with others about the results, will be assessed using several items.

The psychological impact of undergoing testing and receiving personal genomic risk information will be assessed through the Multidimensional Impact of Cancer Risk Assessment (MICRA) [31]. The MICRA consists of three subscales (a) distress (six items), (b) uncertainty (nine items) and (c) positive experiences (four items – reverse scaled) (Table 1).

**Table 1 Tab1:** Multidimensional Impact of Cancer Risk Assessment (MICRA) domain subscales

Distress (6 items)	Feeling upset about my risk information
	Feeling sad about my risk information
	Feeling anxious or nervous about my risk information
	Feeling guilty about my risk information
	Feeling a loss of control
	Having problems enjoying life because of my risk information
Uncertainty (9 items)	Worrying about my risk of getting cancer (or getting cancer again if you have already been diagnosed with cancer)
	Being uncertain about what my risk information means about my cancer risk
	Being uncertain about what my risk information means for my child(ren) and/or family’s cancer risk
	Having difficulty making decisions about cancer screening or prevention (e.g. having preventive surgery or getting medical tests done)
	Feeling frustrated that there are no definite cancer prevention guidelines for me
	Thinking about my risk information has affected my work or family life
	Feeling concerned about how my risk information will affect my insurance status
	Having difficulty talking about my risk information with family members
	Worrying that the genetic counselling and testing process has brought about conflict within my family
Positive experiences (4 items – reverse scaled)	Feeling relieved about my risk information
	Feeling happy about my risk information
	Feeling that my family has been supportive during the genetic counselling and testing process
	Feeling satisfied with family communication about my genetic risk information

Additional MICRA items that are assessed separately to the subscales include: Feeling regret about getting my risk information; and Understanding clearly my choices for melanoma prevention or early detection. In addition, if the participant has a child(ren), two additional items are assessed: Worrying about the possibility of my child(ren) getting melanoma; Feeling guilty about possibly passing on the melanoma risk to my child(ren). If the participant has cancer, or has had it in the past, the following items are also assessed: Feeling that my genetic risk information has made it harder to cope with my cancer; and Feeling that my genetic risk information has made it easier to cope with my cancer. The responses are scored as 0 for ‘never’, 1 for ‘rarely’, 3 for ‘sometimes’ and 5 for ‘often’ for the distress and uncertainty MICRA subscale items; and as 5 for ‘never’, 3 for ‘rarely’, 1 for ‘sometimes’ and 0 for ‘often’ for the positive experiences subscale items. The scores will be summated for each subscale, and the three subscales also summated to give a total score. Higher values of the MICRA score are related to increased experiences of distress. The questionnaire items for the additional MICRA items will be scored the same way as the distress and uncertainty subscales, with the possible range of 0–5 when there is one item, and 0–10 when there are two items.

The Genetic Counselling Satisfaction Survey (GCSS) [32]: *To what extent do you agree with the following statements?*I felt I could talk about my reaction to my risk information with the genetic counsellorThe genetic counsellor helped me to understand my risk information and make decisions about my health careI felt better about my health after talking to the genetic counsellorThe length of the phone call was appropriateThe genetic counsellor was truly concerned about my well beingTalking to the genetic counsellor was valuable to meUnderstanding of genetic risk information, and amount read by participants

Response options are on a 5-point Likert scale: 1 = strongly disagree, 2 = disagree somewhat, 3 = uncertain, 4 = agree somewhat, 5 = agree strongly.
Recall of personal genetic risk categoryCommunication of result with family, friends and health professionalsMotivations and barriers to family communication about genetic risk [33]Satisfaction, understanding and amount read of the personal genetic risk booklet

## Methods

### General study design and plan

The Melanoma Genomics *Managing Your Risk Study* is a parallel-group, two-arm, RCT with a 1:1 allocation ratio. Supplementary Figure 1 shows the schema for the trial.

### Eligibility criteria

Eligible participants met all of the following criteria:
Aged 18–69 years at the time of recruitmentNever had a melanomaSome European ancestry, since current knowledge of genomic variation associated with melanoma risk is based predominately on populations with European ancestry, although there are ongoing efforts to improve this disparity [34]

### Randomisation and blinding

Randomisation occurred once participants had completed their baseline questionnaire and returned their baseline UV dosimeter. Randomisation to the intervention or control arm (allocation ratio 1:1) was conducted independently by the University of Sydney’s NHMRC Clinical Trials Centre Randomisation Service using a computer-based system. The stratified minimisation procedure [35] was used to ensure that the study groups were balanced by:
Traditional phenotypic risk score (low vs. high) [36],Sex (male vs. female),State or territory of residence within Australia, andAge group (18–44 years vs. 45–69 years)

Traditional risk scores were classified as high or low based on a validated published risk prediction model that includes variables for moles (naevi), hair colour, eye colour, artificial sunbed use, first-degree family history of melanoma, and personal history of keratinocyte cancers (e.g. basal cell carcinoma, squamous cell carcinoma) [36]. For the traditional risk score, a cut-point of 1.223 was used to ensure that approximately half of participants were in the low/high-risk groups; this cut-point is based on data from our pilot trial and Australian Melanoma Family Study controls) [13, 36].

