### Sample size

Sample size calculations are based on detecting a 20% difference in the primary outcome of average daily SEDs between intervention and control arms, in each of the low- and the high-risk phenotype groups. There is currently no consensus as to a ‘safe’ daily SED limit. Instead, skin cancer prevention strategies for the public primarily aim to shift the distribution of sun exposures downwards, especially in seasons of peak exposure. Due to the skewed nature of the SED exposure data, the sample size was calculated using a *t* test with a geometric mean ratio (geometric mean SEDs in intervention group/geometric mean SEDs in control group) of 0.8, coefficient of variation 0.9, 80% power and *α* of 0.05.

Based on these calculations, a sample of 756 people (378 in the high-risk phenotype group and 378 in the low-risk phenotype group), split evenly between the intervention and control arms, will provide 80% power to detect a 20% reduction in the primary outcome in favour of the intervention with either low- or high-risk phenotypes. Allowing up to 15% with incomplete follow-up at 12 months, we will need to recruit 892 people (446 in each of intervention and control arms). Secondary analysis pooling the data from the low- and high-risk phenotype groups will give > 97% power to detect a 20% difference in SEDs between the intervention and control groups.

No interim analysis, safety analysis and or data monitoring is planned for this study due to the minimal risks associated with the intervention.

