### Missing data

The number of participants who complete the 12-month follow-up will be described by allocation; the study arms will be compared using chi-square tests and logistic regression to see if the attrition rate differs by arm and to compare baseline characteristics of participants who did and did not complete follow-up. Of those who complete follow-up, each variable will be examined for the presence of missing data and if > 10% is observed for primary or secondary outcomes, then sensitivity analyses will be performed using complete case analysis or multiple imputation methods assuming data are missing at random (MAR). The MAR assumption indicates that the propensity for missingness does not depend on the unobserved outcome but rather is related to some other observed data.

The distribution of dosimeter sun exposure days will be described by study arm. Non-adherence will be defined as participants that fail to wear the dosimeter over at least one day on both a weekday and a weekend. Level of adherence (e.g. number of days worn) will also be described. For participants who do not have UV dosimeter (SED) data for both weekday and weekend exposures, we will estimate their missing exposure using imputation methods based on the participant’s available weekday or weekend SEDs, and SEDs data from the same age-group, gender, traditional (phenotypic) risk group and state or territory.

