### Primary efficacy analysis

Geometric mean score and 95% CI will also be represented graphically from over time (baseline, follow-ups 1 and 2). The primary analysis will be an intention-to-treat comparison of intervention and control arms for mean differences in UVR exposure measured as log-transformed daily SEDs at 12 months. The primary efficacy of the intervention will be assessed in each phenotypic risk group (high and low). UV dosimeter values will be log-transformed because of their right-skew distribution, and log-transformed values will be interpreted as a percentage change in the geometric mean of SEDs/day [41]. An analysis of covariance (ANCOVA), adjusted for baseline values and all randomised stratification factors will be performed [40]. A sensitivity analysis will be conducted on the subgroup of participants (*N* = ~ 240) that will wear a UV dosimeter for 10 days at follow-up 1 (see subheading 'Sensitivity Analysis'); given the repeated nature of the outcomes in this subgroup, generalised linear mixed models (GLMMs) with random intercepts will be fitted to assess the overall intervention effect. The primary analysis will be based on the complete case principle given that the power was adjusted with a conservative loss to follow-up rate of 15%. However, if 10% or more of the randomised patients do not have their primary outcome recorded, a sensitivity analysis will be performed using multiple imputation methods assuming that data are missing at random.

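### A randomised participant with a 12-month SED but no usable baseline SED drops out of the primary ANCOVA as it is written

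*SAP article*

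**What the plan says.** All of the following is in the SAP article.

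- **Randomisation and blinding:** "Randomisation occurred once participants had completed their baseline questionnaire and returned their baseline UV dosimeter". Neither this section nor Eligibility criteria mentions a minimum wear time or a valid reading.
- **Primary efficacy analysis, model:** "An analysis of covariance (ANCOVA), adjusted for baseline values and all randomised stratification factors will be performed".
- **Primary efficacy analysis, missing data:** "The primary analysis will be based on the complete case principle". The reason offered is that the sample size already allows for 15% dropout. A multiple-imputation sensitivity analysis follows "if 10% or more of the randomised patients do not have their primary outcome recorded".
- **Missing data, adherence:** "Non-adherence will be defined as participants that fail to wear the dosimeter over at least one day on both a weekday and a weekend". The number of days worn is also to be described, and the distribution of dosimeter days is given by arm. None of this is limited to one time point.
- **Missing data, imputation:** where weekday and weekend SEDs are not both available, the gap is filled by "imputation methods based on the participant’s available weekday or weekend SEDs", together with SEDs from participants of the same age group, gender, phenotypic risk group and state or territory.
- **Sample size:** the step from 756 to 892 is made by "Allowing up to 15% with incomplete follow-up at 12 months".
- **General considerations for statistical analysis** and **Analysis populations:** all randomised participants are to be analysed, in the arm to which they were assigned.

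**The concern.** A returned badge is not the same as a usable reading. The plan expects some badges not to be worn enough, since it defines non-adherence. The primary model needs a baseline log-SED for every row, and a complete-case fit drops any row without one.

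A person can therefore supply the trial's primary outcome and still be missing from its primary analysis because of a covariate. The other missing-data rules do not clearly reach this person: one is about missing outcomes, one is about loss at 12 months, and one starts from the participant's own partial SED record.

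At stake are the match between the analysis and the all-randomised principle, some precision in each phenotype group (where the primary comparisons are made), and a handling choice that would otherwise be made with the data in hand.

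**Working it through.** **Which rule covers which participant**

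| Baseline dosimeter record | 12-month SED | What the plan as written does |
|---|---|---|
| Weekday and weekend | Observed | Analysed |
| Weekday only or weekend only | Observed | Retained, because the imputation under Missing data is not limited to 12 months |
| No usable SED | Observed | Dropped by the complete-case ANCOVA; not counted by the 10% trigger; not in the 15% allowance |
| Any | Missing | Dropped; counted by the 10% trigger; within the 15% allowance |

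Only the third row is the problem.

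**Reproducing the plan's figures**

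Inputs from Sample size: geometric mean ratio 0.8, coefficient of variation 0.9, power 80%, α 0.05. The test is two-sided (General considerations).

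- Effect on the log scale: |ln 0.8| = 0.2231.
- SD on the log scale: √ln(1 + 0.9²) = √ln 1.81 = 0.7703.
- Noncentral-t power with 189 per arm in a phenotype group: 80.2%. Four such cells give 4 × 189 = 756, as stated.
- Recruitment: 756 / 0.85 = 889.4, which is 890 against the stated 892.
- Pooled power with 378 per arm: 97.8%, in line with the stated figure of above 97%.

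**Effect of unusable baselines**

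The document gives no rate, so the rate m is assumed at 2% to 10%, independent of the 12-month loss. Number analysed = 892 × 0.85 × (1 − m); a quarter of that is the number per arm per phenotype group.

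| m (assumed) | Outcome observed but dropped | Analysed | Per phenotype group | Power per group, unadjusted t test |
|---|---|---|---|---|
| 0 | 0 | 758 | 379 | 80.3% |
| 2% | 15 | 743 | 372 | 79.5% |
| 5% | 38 | 720 | 360 | 78.3% |
| 10% | 76 | 682 | 341 | 76.1% |

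Pooled power stays at 96.6% or more throughout.

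**How far this depends on the assumptions**

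- *Loss below the ceiling.* With 10% loss and 5% unusable baselines, 892 × 0.90 × 0.95 = 763 remain, which is above 756, and power is 80.5%.
- *Gain from ANCOVA.* Adjusting for baseline multiplies the SD by √(1 − ρ²), where ρ is the baseline to 12-month correlation (assumed, not given). In the worst row above, ρ = 0.31 gives an SD of 0.7703 × √(1 − 0.31²) = 0.732 and power of 80.1%. With ρ = 0.5 the SD is 0.667 and power is 86.9%.

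**The case against.** The strongest reply has four parts.

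1. **The sentence on randomisation is about timing.** It does not say that blank or unworn badges were accepted, and checks on return may be described in the protocol, which is not shown. This stands as a limit on how many people are affected. It does not supply the missing rule, because the SAP article itself states the model, the complete-case principle and the trigger.

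2. **The imputation rule may already cover this.** It also draws on SEDs from matched participants, so it could be read as reaching an empty record. This stands in part. Partial baseline records are rescued, and the wording is not fully clear for empty ones. But the rule is phrased as building on the participant's own available SED, and someone with neither a weekday nor a weekend value has none. It would also be wrong to say that baseline non-wear goes unreported: dosimeter days and adherence are described without restriction to 12 months, and the data summaries give non-missing counts by arm.

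3. **No bias is shown.** This stands. A reader might infer that dropping these people distorts the intervention effect. The documents do not support that: the baseline is measured before allocation, so exclusion on it is unrelated to arm.

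4. **The trial is not shown to be underpowered.** This stands too. A reader might infer from the table that 756 will be missed. That follows only if loss reaches the full 15%, which the plan calls conservative, if baseline non-wear is independent of later loss, and if power is judged by an unadjusted t test that is not the primary model.

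**Conclusion.** The point holds as a gap in the definition of the primary analysis set. Followed as written, the plan leaves out a randomised participant with an observed primary outcome and no usable baseline SED, contrary to its own all-randomised principle.

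The cost is precision, not bias. The number affected is unknown and probably small. At an assumed 2% to 10% on top of the full 15% loss, the cost is about 1 to 4 percentage points of unadjusted power per phenotype group (80.3% down to between 79.5% and 76.1%). A modest baseline to 12-month correlation would recover this. The case for change therefore rests on consistency and on fixing the rule in advance, with power a secondary reason. The change is worth making because the exclusion is avoidable at almost no cost.

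**What to change.** In Primary efficacy analysis:

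- Define the primary analysis set as all randomised participants with a 12-month SED.
- State that the weekday/weekend imputation under Missing data also applies to the baseline record.
- Where baseline log-SED is wholly missing, fill the covariate with a value derived without reference to arm or outcome. Examples are the mean of the matched age, sex, phenotypic risk and state group, or of the phenotypic risk group. Add a missing-baseline indicator if numbers allow.
- Report by arm the number handled in this way.

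Apply the same rule to the other dosimeter-based ANCOVAs (time-specific UV exposure). Questionnaire outcomes have less need of it, since a completed baseline questionnaire was required before randomisation.

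The cost is a few sentences in the SAP and a few lines of code, with no new data. The one drawback is that these participants contribute without a personal baseline adjustment.

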### Study variables

Outcomes will be measured at baseline, 1 month after receipt of the booklet/s (except dosimeter outcomes that were only assessed for a subset of participants at 1 month), and again 12 months after baseline as summarised in Table 2. A sample of ~ 240 participants will wear a UV dosimeter for 10 days at follow-up 1 (1 month after receipt of booklet/s).

**Table 2 Tab2:** Schedule of study parameters and collection time points

	Study period				
	Screening/consent	Baseline/randomisation	Intervention delivery	Follow-up^**a**^	
Time point	***-1***	0	***T1***	***F1***	***F2***
**Enrolment:**					
Eligibility screen	X				
Informed consent	X				
Allocation		X			
**Group allocation:**					
***Intervention arm:***					
Saliva sample		X			
Personalised melanoma genetic risk booklet			X		
Phone call from genetic counsellor			X		
Educational booklet on melanoma preventive behaviours			X		
***Control arm:***					
Educational booklet on melanoma preventive behaviours			X		
**Assessments** (control and intervention patients)**:**					
Demographics		X			
Melanoma risk factors		X			
Sun exposure (objective measure)		X		X^b^	X
Sun exposure (self-report)		X		X	X
Sun-protection behaviours		X		X	X
Skin examination behaviours		X		X	X
Intentions, beliefs and attitudes towards sun-protection behaviours and skin examinations		X		X	X
Discussion about sun protection and skin examinations with family		X		X	X
Perceived social norms about sun protection and skin examination		X			
Perceived melanoma risk		X		X	X
Skin-cancer related worry		X		X	X
Perceived control over the development and early detection of future melanomas		X		X	X
Risk taking behaviours (Domain-Specific Risk-taking scale (DOSPERT))		X			
Psychological distress and well-being (MHI-5)		X		X	X
Confidence in completing medical forms		X			
General health		X			
Satisfaction with educational booklet on melanoma preventive behaviours, and amount read by participants				X	X
Out-of-pocket costs for sun-protection items				X	X
Visits to health care professionals				X	X
Private health insurance				X	X
Use of medications that may increase risk of melanoma or skin sensitivity to sunlight		X		X	X
Importance of health		X			
Confidence in understanding medical information		X			
Reasons for participating in the study		X			
Receiving advice from health professional regarding sun protection and skin checks		X		X	X
Information seeking about skin cancer and genetics		X		X	X
Use of the study website		X		X	X
Use of applications related to sun protection or skin examinations					X
***Measures related to receiving genetic risk information (intervention participants only)*****:**					
Recalling personal genetic risk				X	X
Communication with family, friends and health professionals about genetic risk				X	X
Motivation and barriers to communication about genetic risk				X	X
Satisfaction with genetic risk booklet and genetic counselling				X	X
Understanding of genetic risk information, and amount read by participants				X	X
Multidimensional impact of cancer risk assessment				X	X

^a^Follow-up 1 (F1) takes place 1 month after participants receive their booklets. Follow-up 2 (F2) takes place 12 months after participants complete the baseline assessment (baseline questionnaire and ultraviolet radiation (UV) dosimeter)

^b^The UV dosimeter measurement will be measured in ~ 240 participants rather than in all participants at the short-term (1-month) follow-up

